### Study Outcomes

This study has 2 types of outcome assessments: outcomes associated with terminal states, such as the percentage of patients or time that it takes to get to a terminal state, and outcomes associated with pathways, such as achievement of guideline-concordant care (Table 2, Multimedia Appendix 1). Terminal states are explicitly modeled as states in MSMs, whereas the probability of receiving guideline-concordant care is derived from estimated transition probabilities (see subsection Aim 2. Generate Data-Driven Insights to Improve Care Delivery Using Estimated MSMs under the Statistical Analysis section).

### Covariates

#### Sociodemographic Characteristics

Patient sociodemographic and clinical characteristics include both time-invariant and time-varying measures and will be used to describe the analytic sample. In addition, they may be used as covariates in MSMs. Planned demographic characteristics include age, race or ethnicity, sex, and insurance history (eg, Medicaid, Medicare, employer-based, or individual or family plans purchased through WA state’s health plan marketplace). Demographics are typically collected at enrollment and confirmed or updated at health care visits over time [48]. Socioeconomic status will be approximated from census block-level measures from the AHRQ SDOH Database [49]. Additionally, clinician-documented housing instability *ICD* (*International Classification of Diseases*) codes are from patients’ EHR data [50], and patients’ inability to pay for care is measured by a recent request to the KP Medical Financial Assistance program for low-income or uninsured individuals [51]. Medical morbidity [52,53], depression [54], anxiety [55], and serious mental illness [56] will be defined by *ICD* codes. AHRQ SDOH database measures will be linked to patient-level records at the county level based on patient addresses.

#### SUD-Related Health Conditions

SUD-related health conditions will be used to describe the analytic sample and as time-varying covariates in the MSMs. These include documented diagnoses for health conditions in which substance use is always the cause (eg, alcoholic gastritis, alcohol neuropathy, accidental drug poisoning, and nonfatal alcohol and illicit drug overdoses). These are measured using *ICD* codes specified by the Centers for Disease Control and Prevention’s Alcohol-Related Disease Impact codes [46,57] and the HEDIS diagnosis grouping of “unintentional drug overdose.”

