### MSM Setup

Data required for fitting MSMs include care occurrences and corresponding event times to characterize state occupancy and transitions over time, along with time-invariant and time-varying covariates. SUD-related medical conditions will be incorporated as covariates when they are expected to influence care type or care setting. Additional details are provided in the analysis section. The time scale for the MSMs is continuous calendar time, with time since entry into each state reset to 0 (“clock reset”) at state entry for modeling transition intensities.

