For simplicity, we omit transition-specific subscripts for the parameters $\left(\eta ,k_{0},\beta \right)$. In the model, $s(\log(t)|\eta ,k_{0})=\sum_{i=1}^{k_{0}}\eta_{i}B_{i}(\log(t))$ represents the log cumulative baseline intensity function, which we model flexibly using restricted cubic spline basis functions (also known as natural cubic splines) $B_{i}(\cdot )$, with corresponding coefficients $\eta_{i}$. The number of knots, $k_{0}$, determines the number of basis functions and thus the flexibility of the baseline intensity functions. For covariates *z*_*i*_(*t*), the coefficients β represent the log hazard ratios at time t. The unknown parameters to be estimated or selected from data are $\left(\eta ,k_{0},\beta \right)$. We will use the Akaike information criterion based on data to select the number of knots, with lower Akaike information criterion values indicating better model fit. The regression coefficient parameters (η,β) will be estimated by using the maximum likelihood approach for statistical inference [62,63]. For each transition, we will include prespecified covariates for adjustment when the number of transitions allows (at least 10 transition events per covariate), and if additional covariate selection is required, variables that are statistically significant at the 5% level based on Wald tests will be included [64]. The estimated transition intensities are transformed to a transition probability from states j to k at time t since entry into state j at time s (s<t, s and *t*>0), by integrating, $p_{jk}(s,t)=\exp\left\{-\int_{s}^{t}q_{jk}(u,z(u))\;du\right\}$.

Multiple incident SUD events may be observed within the same patient (see Quantitative Study Population). For example, a patient may have an incident SUD event, eventually experience a terminal state such as ceasing SUD care (eg, one who receives no SUD care for 194 days), and then experience a second incident SUD event. Including multiple incident events from the same patient within the same subcohort in the MSM framework may introduce within-patient correlation and reflect care pathways that differ from those of the initial episode. We will account for within-patient correlation using a sandwich variance estimator for the parameter estimates. The number of prior incident events will be included as a covariate or used as a stratification factor, depending on its distribution.

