How do answers for the above key questions differ across patient characteristics? First, overall quantities will be estimated to address the key questions in Table 4. Then, Cox proportional hazards models will be fit for each transition intensity to assess associations between patient characteristics, such as demographics, SUD type and severity, mental health diagnosis, socioeconomic status, and transition intensities [9]. Using the fitted model, the quantities required to address the questions in Table 4 will be calculated as a function of patient characteristics included in the transition models.

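### Predicted probabilities from transition models containing SUD-related conditions as time-varying covariates are not defined as written, because the future path of those covariates is random and not modelled

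*Protocol article*

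**What the plan says.** Under Covariates, SUD-Related Health Conditions, the article gives these diagnoses two uses: "SUD-related health conditions will be used to describe the analytic sample and as time-varying covariates in the MSMs". Its examples include "accidental drug poisoning, and nonfatal alcohol and illicit drug overdoses".

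Inclusion is conditional. MSM Setup says "SUD-related medical conditions will be incorporated as covariates when they are expected to influence care type or care setting". The Aim 1 methods add an event-count condition: "we will include prespecified covariates for adjustment when the number of transitions allows (at least 10 transition events per covariate").

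Also under Aim 1, the intensity is written q_jk(t,z(t)), and "The estimated transition intensities are transformed to a transition probability from states j to k at time t since entry into state j". The integrand is q_jk(u,z(u)) for u running from s to t, so covariate values after s are needed.

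Aim 2 relies on this step. Study Outcomes says "the probability of receiving guideline-concordant care is derived from estimated transition probabilities". Table 4 lists transition probabilities, hitting probabilities, expected first passage times and expected numbers of visits. For differences across patient characteristics, Aim 2 says "the quantities required to address the questions in Table 4 will be calculated as a function of patient characteristics included in the transition models".

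**The concern.** Overdose, alcoholic gastritis and similar diagnoses arise in the patient's own course and are recorded only while the patient is alive and in contact with care. They are internal covariates. A model for q(t,z(t)) describes the hazard given the history so far. It gives a probability over a future interval only if z over that interval is fixed by assumption or averaged over a model for z. The article does neither for the Table 4 outputs.

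The simplest software default holds z at its current value, which assumes that no patient free of the condition ever develops it. Plugging in observed paths instead conditions on the future. Some Table 4 outputs, such as the probability of ever reaching a state, have no fixed horizon, so the assumption has to hold indefinitely.

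Subgroup predictions are exposed in a second way. If two SUD types differ mainly in how often overdose occurs later, a prediction with z frozen shows no difference between them.

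There is also a timing issue. Care states are built from the same encounters and diagnosis codes that record these conditions, so an unlagged covariate can switch on at the very encounter that is the transition.

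**Working it through.** **Inputs.** The article gives no onset rate, hazard ratio, exit rate or predicted probability that bears on this, so there is no stated figure to reproduce. Everything below is an assumed illustration: one state with one exit, 30-day exit probability 10% or 30% without the condition, onset 2%, 5% or 20% per 180 days, hazard ratio (HR) 0.5, 2 or 4.

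**Formula.** Exit hazard is h0 before onset and h1 = HR × h0 after it; onset rate is λ. Averaged over the random path of z,

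S(T) = exp(−(h0+λ)T) + λ[exp(−h1·T) − exp(−(h0+λ)T)] / (h0+λ−h1).

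True exit probability is 1 − S(T). With z frozen at 0 it is 1 − exp(−h0·T).

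**Worked case (10% per 30 days, onset 20% per 180 days, HR 2, T = 180).**
- h0 = −ln(0.9)/30 = 0.003512; λ = −ln(0.8)/180 = 0.001240; h1 = 0.007024.
- exp(−(h0+λ)T) = 0.4252; exp(−h1·T) = 0.2824; second term = 0.0779.
- S = 0.5030, so the true exit probability is 49.7%.
- Frozen at 0: 1 − 0.9^6 = 46.9%, which is 2.8 points too low.

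**Range with z frozen at 0** (10% per 30 days unless stated).

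| Onset per 180 days | HR | Horizon (days) | True | Frozen | Error (points) |
|---|---|---|---|---|---|
| 2% | 2 | 30 | 10.02% | 10.00% | −0.02 |
| 5% | 4 | 180 | 48.3% | 46.9% | −1.5 |
| 20% | 4 | 180 | 52.9% | 46.9% | −6.0 |
| 20% | 0.5 | 180 | 44.9% | 46.9% | +1.9 |
| 20%, exit 30% per 30 days | 4 | 30 | 31.0% | 30.0% | −1.0 |

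With onset of 2% to 5%, the 30-day error is about 0.2 points or less throughout. Freezing z at 1 for the whole interval misses the average by about 5 to 46 points.

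**Subgroups.** Take two groups with the same hazards given z, but onset of 5% against 20% per 180 days. At 180 days (10% per 30 days) the true difference is 44.91 − 46.38 = −1.5 points for HR 0.5, 49.70 − 47.55 = +2.1 for HR 2, and 52.88 − 48.33 = about +4.5 for HR 4. Frozen z gives zero in each case. At 30 days, over both exit rates, the true difference is 0.8 points or less in size.

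**Longer horizon, separate assumptions.** With h0 = 0.30/year, HR 4 and T = 1 year, onset of 0.02, 0.10, 0.30 and 0.50/year gives 26.4%, 28.4%, 32.7% and 36.6%, against 25.9% frozen. With onset of 0.30/year, the same inputs give 2.5% against 2.4% at 30 days and 7.8% against 7.1% at 90 days.

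**What is not harmed.** In a simulation of 400,000 patients with true HR 2, the time-dependent estimate of the HR was 2.00. The covariate-free 180-day exit probability was 49.8% against a true 49.7%. Only the frozen-z prediction missed.

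**The case against.** A reader might infer that the Aim 2 probabilities and subgroup differences as a whole are wrong. The documents do not support that:

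- Aim 2 says overall quantities are estimated first and covariate models follow. If the first step leaves these covariates out, those quantities are sound.
- Terminal-state comparisons across SUD types are descriptive and need no path for z. Stratified analyses by SUD type are also considered.
- Inclusion depends on expected influence and on event counts, so not every transition model will contain these conditions. The characteristics named as examples for the subgroup models do not list them, although SUD severity may overlap.
- Nowhere does the article say z will be frozen. Averaging over a model for z, adding a state, or reporting a stated scenario are all valid. Sequence probabilities are to use hypothetical scenarios detailed in an appendix not shown.
- The error need not understate risk. For a transition that the condition makes less likely, the sign reverses.
- The Limitations section disclaims causal interpretation, so losing an indirect effect is not in itself a breach of the stated aims.
- The prediction horizons named are mostly 7 to 90 days, where the illustrated error is small.

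All of this stands and limits the point. It does not remove it. The article itself fixes both the time-varying coding and the integral over z(u). It points to the scenario appendix for sequence probabilities and does not say that it covers the Table 4 outputs or their versions by patient characteristics. The inclusion rule also favours transitions where the condition is expected to matter, which is where its future path cannot be ignored.

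**Conclusion.** The point holds in a limited form. For any transition model that includes SUD-related conditions as time-varying covariates, the stated conversion does not define a predicted probability, hitting probability, passage time or subgroup version of these. Holding z at its current value gives a biased answer, with direction set by the hazard ratio.

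Hazard ratios, quantities from models without these covariates, and the descriptive terminal-state comparisons are not affected.

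The size cannot be determined from the article. Under the assumed inputs it is negligible at 7 to 30 days with rare onset. At 180 days or more, with frequent onset and a strong effect, it reaches several points, and subgroup differences that act through later onset can vanish. These figures rest on a single state with constant rates and on onset rates and hazard ratios that the article does not supply.

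**What to change.** In the transition models that feed Aim 2 predictions, code SUD-related conditions at the index date from a fixed look-back, or leave them out.

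Keep the time-varying version as a separate association model reporting hazard ratios only. Lag the covariate there, so that the encounter recording the condition is not itself the transition being predicted.

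If a probability is nevertheless taken from the time-varying version, label it as conditional on a stated covariate path, or average it over a model for the condition.

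The cost is one more model specification. The downside is that the main predictions will not use condition status updated during the episode, including an overdose that may change later care.

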### Statistical Analyses

#### Aim 1: Apply MSMs to Comprehensively Characterize SUD Care Transitions

Separate MSMs will be run for each of the 5 subcohorts specified in Table 1. The 5 subcohorts are mutually exclusive. All prespecified states that are anticipated will be considered. States may be collapsed to address states with a small number of events, and new states may emerge if they occur with sufficient frequency (eg, concurrent receipt of pharmacotherapy and behavioral treatment and counseling). When collapsing or expanding states, we will strike a balance between clinical interpretability and reliable parameter estimation. As a general guideline, ≥40‐50 transition events from *S*_*j*_ to *S_j_* per covariate helps ensure stable hazard ratio estimates and corresponding SEs, but if collapsing states compromises the clinical interpretability of the results, we will adopt a more permissive threshold of at least 10 transition events per covariate for modeling [58]. This criterion will first be applied to define states; specifically, a minimum of 40 (or 10 under the more permissive threshold) transition events is required to define a state, allowing inclusion of 1 covariate in the transition model. When transitions are sufficient to include covariates in the model, at least 40 × *m* transition events are required. Covariate selection for each transition model, given the number of transitions, is described below. Follow-up time or care episode duration is defined as the interval from entry into the initial state (time 0) to entry into a terminal state.

Figure 1 provides a graphical representation of a simplified MSM illustrating potential care pathways. In this example, patients who meet the inclusion criteria and are identified as having an incident SUD in primary care enter the initial state *C*_1_. Patients then transit into 1 of 15 care states (*S*_1_, ... ,*S*_15_) defined by a service type and setting. From these states, patients may transition to temporary discontinuation of care, *D*, or an SUD remission state, *R*. Transitions between the transient states (care states, temporary discontinuation, and SUD remission) are bidirectional, whereas any transition to a terminal state (*T*_1_, ..., *T*_4_) is unidirectional, reflecting that patients cannot leave terminal states once they are entered in MSMs. At the end of follow-up, patients occupy 1 of the 4 terminal states.

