**Methods:**

Quantitative data sources will include electronic health care records, insurance claims, self-reported measures of substance use and SUD symptoms, and death data from an integrated health care system in Washington State. To identify care pathways, we will apply continuous time, multistate modeling methods to empirically observe the longitudinal course of SUD care transitions undertaken by patients over time; each “state” or occurrence of care will be characterized by the intervention received (eg, evaluation or assessment, behavioral treatment or counseling, and pharmacotherapy) and setting of care (eg, outpatient, intensive outpatient, or inpatient or residential). The estimated parameters from the fitted MSMs will be transformed or interpreted to characterize SUD care quality, such as wait times for SUD visits, and receiving an adequate psychotherapy dose. To compare outcomes associated with care pathways, we will examine terminal states, including death and loss to follow-up. Using a mixed methods design, we will sample and interview patients engaged in empirically derived pathways to understand their care experiences, observe and interview clinicians to elucidate health system factors that impact SUD care transitions, and integrate qualitative and quantitative findings using joint displays.

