### States for the MSMs

States will capture 3 types of events related to SUD care: initial states, transient states, and terminal states. Defining states requires a balance of specificity to produce actionable information, and parsimony to allow for an estimable statistical model with accurate estimates and smaller SEs.

Initial states in the MSMs represent the clinical settings that triggered an incident event at the start of an SUD care episode, corresponding to the 5 subcohorts in Table 1.

There are 3 types of transient states. The first type is care states, which include different types of care provided in the health care system to treat the SUD, defined by combinations of setting and service type (Table 2). We opted to define 15 preliminary SUD care states based on a combination of 3 settings and 5 service types. The second type of transient state is temporary discontinuation of care. Entry into the temporary discontinuation care state is triggered using a clinically meaningful threshold for time elapsed between SUD treatment visits. The last transient state is SUD remission, which represents an improvement in the patients’ disease.

**Table 2. T2:** Transient states and terminal states are represented in the multistate models.

Category	States included	Description
Transient states	A total of 17 transient states include 15 care states derived from crossing 5 service types with 3 care settings; temporary discontinuation of SUD^a^ care; and remission of use disorder.	Care states Service types Evaluation and assessment Behavioral treatment and counseling Prevention, education, and case management Pharmacotherapy Other service Settings Outpatient Intensive outpatient Inpatient or residential Other transient states Discontinuation of SUD care A lack of SUD care over a specified period^b^ Remission of use disorder Low risk score on alcohol and substance use screen; clinically meaningful reduction on screening scores or <2 symptoms on *DSM-5*^c^ checklist; SUD remission diagnosis
Terminal states	4 states representing the end of a care episode	Death, derived from dates in health care enrollment records or Washington State death data Loss to follow-up, defined as at least 31 days without KPWA insurance coverages Ceased SUD care (no medication fills or services with a qualifying SUD diagnosis for more than 194 days Administrative censoring (in the middle of a care episode when data collection ends)

a SUD: substance use disorder.

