b Temporary discontinuation will be defined separately for each care state using an appropriate threshold for time elapsed between visits that reflects acceptable gaps in care for that specific state. All of these periods will be shorter than 194 days to distinguish temporary discontinuation from ceasing substance use disorder care.

c *DSM-5*: *Diagnostic and Statistical Manual of Mental Disorders, Fifth Edition*.

Terminal states indicate the end of an SUD care episode (Table 2), such as ceasing SUD care.

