#### Death Data

Death, classified as a terminal state in the MSM, will be ascertained from the Washington State Department of Health death data. These data are available for all patients, regardless of whether they remain enrolled in the health system. Following standard practice [47], death data are triangulated from several data sources. Reliability of death date (excellent, fair, or poor) is determined based on the source, the number of reporting sources, and the strength of the match in the matching process (eg, no discrepancies in identifiers).

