How often and where is guideline-concordant care achieved? We will analyze several health care quality measures, including those published by the National Committee on Quality Assurance [36,70,71] and others [72,73]. These monitor initiation of care, or the receipt of prespecified health services following an incident SUD event; engagement in care, defined as having a minimum number of qualifying services after initiating care; and adequacy of treatment, which captures whether quantity or duration of treatment over time is sufficient. Achievement of these measures can be ascertained from the states in the MSM model. Multimedia Appendix 1 contains details about how we will operationalize these quality measures using estimates from the fitted MSMs. For example, a National Committee on Quality Assurance quality measure monitors follow-up for patients who have an acute care encounter for SUD. This measure monitors the percentage of patients who obtain follow-up SUD care after an ED visit over 7-day and 30-day timeframes. Thus, among patients in the ED and hospitalizations subcohort whose incident SUD event is in an ED setting, we will estimate transition probabilities capturing the likelihood of transitioning from the initial state to any SUD care state within 7-day or 30-day. We will estimate measures reflecting care engagement and adequacy of treatment by estimating the expected length of time in a pharmacotherapy state or the expected number of visits to qualifying states over the duration of time specified in Multimedia Appendix 1.

How does the probability of occupying terminal states differ across patient subgroups? Within study subcohorts, we will conduct descriptive analysis comparing occurrences of terminal states across patient subgroups. For instance, we will compare terminal states at selected time points (eg, 1-year after cohort entry) across mutually exclusive subgroups defined by patient SUD type (eg, sole opioid, alcohol, or cannabis use disorder vs multiple SUDs). Comparisons of terminal states will help provide insights into whether outcomes differ for specific groups of patients who have incident SUD events in each setting [28].

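### Ceased care and loss to follow-up are absorbing and compete with death, so the modelled death probability is death before disengagement, not mortality by a fixed time after cohort entry

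*Protocol article*

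**What the plan says.** Table 2 of the protocol article lists four terminal states. Beside death and administrative censoring stand "Loss to follow-up, defined as at least 31 days without KPWA insurance coverages" and "Ceased SUD care (no medication fills or services with a qualifying SUD diagnosis for more than 194 days". Under Aim 1 of the Statistical Analyses, transitions into these states run one way, "reflecting that patients cannot leave terminal states once they are entered in MSMs". Follow-up is "the interval from entry into the initial state (time 0) to entry into a terminal state", and every patient ends in one of the four.

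Shorter gaps are handled separately. Temporary discontinuation is a transient state with state-specific thresholds: "All of these periods will be shorter than 194 days to distinguish temporary discontinuation from ceasing substance use disorder care". A patient who ceased care can also return through a second incident event, which opens a new episode (end of the Aim 1 model description).

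On death data, the Death Data section says "These data are available for all patients, regardless of whether they remain enrolled in the health system". Quantitative Data Sources limits the state file to deaths occurring in Washington.

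On use, the Abstract says "To compare outcomes associated with care pathways, we will examine terminal states, including death and loss to follow-up". For patient subgroups, Aim 2 says "we will compare terminal states at selected time points (eg, 1-year after cohort entry", closing the parenthesis there. Aim 3 samples two pathways with a high probability of negative terminal states, giving death as the example.

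**The concern.** Because no transition leads from ceased care or loss to follow-up to death, time at risk of a counted death stops at disengagement. A patient who drops out and dies some months later is recorded as ceased or lost, even where the linked file shows the death. The article describes no mortality analysis beyond those states, and its Limitations section does not mention the point.

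The quantity the model yields is thus the probability of dying before disengaging, with disengagement as a competing event. A table of terminal states at 1 year after cohort entry invites a different reading, namely mortality by 1 year. The gap between the two depends on retention, which is what differs between the pathways and subgroups being compared. A comparison of death across them therefore mixes mortality with retention.

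**Working it through.** The article states no death rate, exit share or event count on this point, so there is no figure of the plan to reproduce. The rates below are assumptions. Only the 31-day and 194-day definitions and the 1-year example come from the article.

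**Check 1: equal mortality, exits at one time.** Assume the same low, constant death rate in and out of care, so that deaths accrue evenly over a horizon of T days. A share e exits on day x, and nobody re-enters.

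- Part of the horizon after exit: f = (T − x)/T.
- Share of deaths not counted: e × f.
- Apparent death ratio, 80% exit against 30% exit: (1 − 0.8f)/(1 − 0.3f). The true ratio is 1.

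| Exit day | Horizon | f | Missed if e = 0.6 | Apparent ratio |
|---|---|---|---|---|
| 200 | 365 days | 165/365 = 0.452 | 27% | 0.638/0.864 = 0.74 |
| 300 | 365 days | 65/365 = 0.178 | 11% | 0.858/0.947 = 0.91 |
| 200 | 1096 days | 896/1096 = 0.818 | 49% | 0.346/0.755 = 0.46 |
| 300 | 1096 days | 796/1096 = 0.726 | 44% | 0.419/0.782 = 0.54 |

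If ceased care is dated at the end of the gap, exit at day 200 by that route needs the last SUD service by about day 6 (200 − 194), and exit at day 300 by about day 106. Loss of coverage can occur earlier. Since true mortality is equal here, this check shows distortion but cannot show reversal.

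**Check 2: mortality allowed to rise after leaving care.** A cohort model moves patients from care, through a gap in which deaths still count, to an absorbed state in which deaths occur but do not count. Assumptions: death rate 0.01 per year in care; 0.01, 0.02 or 0.04 per year after leaving; leaving care at 0.3 per year (slow) or 3 per year (fast); gap of 0, 31 or 194 days; horizons of 1, 3 and 5 years; no re-entry. The contrast is strong: ignoring deaths, 1 − exp(−0.3) = 26% against 1 − exp(−3) = 95% leave within a year. Selected results, counted deaths / all deaths:

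| Gap | Horizon | Rate after leaving | Slow loss | Fast loss |
|---|---|---|---|---|
| 31 days | 1 year | 0.02 | 0.90% / 1.13% | 0.48% / 1.67% |
| 31 days | 3 years | 0.02 | 2.05% / 3.94% | 0.50% / 5.51% |
| 194 days | 1 year | 0.01 | 0.96% / 1.00% | 0.78% / 1.00% |
| 194 days | 1 year | 0.02 | 1.07% / 1.13% | 1.24% / 1.67% |
| 194 days | 1 year | 0.04 | 1.27% / 1.39% | 2.16% / 3.00% |
| 194 days | 3 years | 0.02 | 2.54% / 3.94% | 1.38% / 5.51% |

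In all 27 combinations the counted figure is below the true one for both pathways. In 25, the fast-loss pathway shows fewer counted deaths although its true mortality is equal or higher. The two exceptions are the 1-year, 194-day rows with rates 0.02 and 0.04: there the order is right, but fast-loss deaths are still undercounted.

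**The case against.** The article's unit is the care episode, and terminal states mark its end. Death before disengagement is a legitimate competing-event quantity, and the intensities of death from care states are not biased merely because follow-up stops at another terminal state. The study is exploratory and disclaims causal interpretation. Nor is poor retention hidden: ceased care and loss to follow-up are reported outcomes, so a pathway that loses patients quickly would show this beside any low death probability. All of that stands. It does not recover the missing deaths, and it does not make the quantity mortality at 1 year.

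Three stronger readings are tempting, and the documents do not support them:

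- *Deaths after disengagement are never counted.* Deaths during the gap may count if the terminal state is dated at the gap's end, which the article does not fix. Deaths after a new incident event count in the new episode.
- *The death file covers everyone.* The Death Data section says all patients, but the state file holds only deaths in Washington.
- *Pathways with poor retention will look safest.* This is a risk that depends on rates, gap and horizon. It fails in two combinations at the article's own example horizon of 1 year.

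An effect on Aim 3 sampling is also not established. Negative terminal states are plural there, with death as an example. If disengagement counts as negative, pathways that lose patients fast become more likely to be sampled, not less.

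**Conclusion.** The point holds in limited form. Followed as written, the model's cumulative probability of the death state is death before disengagement. Used as mortality by a fixed time since cohort entry, it is too low, generally by more where retention is poorer, and comparisons across pathways and subgroups can be distorted. Reversal occurs under some assumed rates and not under others; it should not be presented as a certainty.

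The size is unknown from the documents. In the equal-mortality illustration the apparent 1-year ratio moves from 0.74 to 0.91 when the assumed exit day moves from 200 to 300, so neither figure is an estimate for this study. Both checks ignore re-entry. This is more than missing detail: the terminal-state structure is stated, and data that allow a correction are already planned.

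**What to change.** Keep ceased care and loss to follow-up as ends of the care episode for all other purposes. Then:

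1. Label the present quantity as death before disengagement wherever it is reported, including the pathway and subgroup comparisons.
2. Add all-cause mortality at fixed times from cohort entry from the linked death data, censored at the end of the death file, with each patient's death counted once.
3. Equivalently, add transitions to death from ceased care and from loss to follow-up, again censored at the end of the death file. A patient must leave the ceased or lost risk set when a new episode starts; otherwise one death could count in two episodes.
4. For Aim 3, state which terminal states are treated as negative.

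The cost is small, because the data are already planned and the episode definition does not change. The downside is that patients who leave coverage and then die outside Washington may be treated as alive. State this as a limitation and add a sensitivity analysis that censors at disenrolment.
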